### Interim analyses {21b}

We will conduct interim DID regression analyses on the primary and secondary outcomes at the endline and follow-up time periods of Cohort 1 and Cohort 2. Final analyses will be conducted on the full dataset after the end of the intervention for all study cohorts (i.e., after Cohort 3 endline and again at Cohort 3 follow-up).

### Methods for additional analyses (e.g., subgroup analyses) {20b}

For each trial cohort (i.e., data collection cohorts), hierarchical random effects models will be estimated to understand variation or treatment effects heterogeneity at the regional- and sub-county levels. After the full data collection is complete (i.e., after data collection on all three trial cohorts is completed), stratified analyses by region will be conducted to provide policymakers and program implementers more detailed information on intervention effects given hypothesized differentials in socio-cultural norms by geographic region. When assessing outcomes at a regional level, the index indicators will be estimated within 10% precision. In addition, we will conduct exploratory sub-group analyses on key covariates including the following: age of the young father, duration of time living with spouse/partner, age and sex of the child, alcohol consumption, and education level of father and spouse/partner.

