**Methods:**

To assess the REAL Fathers intervention, we use a cluster-randomized controlled trial design within 48 sub-counties randomly sampled from 24 districts in six regions of Uganda. Sub-counties were randomly allocated to treatment or control arms at baseline. Study participants are fathers ages 16–25 years and their cohabitating wives whose eldest child is below the age of 3 years (*n* = 3744 couple dyads). Primary outcomes are the following: (1) reduced intimate partner violence; (2) reduced violent discipline of children; (3) increased father-child engagement and play; (4) improved early childhood development. Secondary outcomes include the following: (1) father’s knowledge of and (2) attitudes towards positive parenting and discipline; (3) father’s use of positive parenting and discipline; (4) father’s use of emotional engagement with child; (5) couple communication and conflict resolution; (6) gender equitable household and caregiving decision-making and behaviors; (7) father engagement in child health-promoting activities; (8) improved knowledge of family planning methods; (9) reduced unmet need for family planning; (10) reduced problem alcohol use; and (11) supportive community norms for father-child engagement and play. Longitudinal survey data will be collected by trained enumerators using KoboCollect in six local languages at three time points: one month before the intervention (baseline); one month after the intervention (endline); and nine months after the intervention (follow-up). Intervention effects on primary and secondary outcomes will be assessed using difference-in-differences (DiD) mixed-effects models that account for the clustered design.

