## Methods: participants, interventions, and outcomes

### Study setting {9}

The study will be conducted in 24 districts across six regions of Uganda (four districts in each region—Fig. 2). The regions and districts include those not previously reached in pilot trials of the REAL Fathers intervention and are as follows:1) Ankole Region: Ibanda, Mbarara, Isingiro, and Rubirizi districts [Implementing Partner: FAWE Uganda Chapter]2) Buganda Region: Kayunga, Buikwe, Luweero, and Nakasongola districts [Somero Uganda]3) Bunyoro Region: Hoima, Kikuube, Kiryandongo, and Masindi districts [Bantwana Initiative Uganda]4) Busoga Region: Kamuli, Bugiri, Iganga, and Mayuge districts [Somero Uganda]5) Lango Region: Dokolo, Kole, Lira, and Oyam districts [All Nations Child Development Centre]6) Teso Region: Amuria, Katakwi, Serere, and Soroti districts [Bantwana Initiative Uganda]

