## Assignment of interventions: allocation

### Sequence generation {16a}

The study will be implemented in 24 districts in six geographical regions of Uganda. As noted above, in each district, a simple random sample of two sub-counties will be taken. These sub-counties will be randomly allocated to either the treatment or control condition (1:1 within each district) using the Mersenne Twister algorithm via the RAND function in Microsoft Excel [52]. For subsequent follow-up studies (midline and endline), all enrolled participants will be re-interviewed at midline and endline surveys. (See Table 7 for sample randomization of sub-counties data).

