## Statistical methods

### Statistical methods for primary and secondary outcomes {20a}

The primary analysis will follow an intention-to-treat (ITT) approach, where all study participants will be analyzed according to their original randomization assignment at baseline. To evaluate intervention effects on primary and secondary outcomes, we will employ difference-in-differences (DID) regression models, which are well-suited for analyzing longitudinal data. DID estimation estimates the causal effect of the intervention by comparing changes in outcomes over time between the treatment and control groups while controlling for unobserved time-invariant characteristics, provided the parallel trends assumption and the Stable Unit Treatment Value Assumption (SUTVA) hold. To account for the complex survey design, we will incorporate random effects in the DID regression models to address clustering at the sub-county level (the unit of randomization). Additionally, clustered standard errors will be used to correct for within-individual autocorrelation and intra-cluster correlation (ICC) at the village level. Where necessary, sample survey weights will be applied to adjust for any imbalances in sub-county or district-level characteristics. As noted above in the “Sample size” section on sample size, we apply Bonferroni correction to account for multiple comparisons in primary outcomes while maintaining an overall 5% level of statistical significance for the trial.

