The trial is also powered to stratify analyses by region with the aim of providing policymakers and program implementers more granular information on which to base regional-level programming and policies in response to differentials in socio-cultural norms by geographic region. The trial will also examine additional questions of for whom the intervention works by testing for interaction by age of the young father, duration of time living with a female partner, age and sex of the child, alcohol consumption, and education level of the father and female partner. These outcome data will be complemented by extensive routine monitoring data collected by implementing partners throughout the project cycle to assess fidelity, refine training and delivery, and strengthen implementation quality to maximize effectiveness in achieving the intended outcomes along the theory of change. In addition to generating evidence on ‘what works’ and ‘for whom’ in prevention programming, data generated from this longitudinal cRCT will also allow, for the first time, an examination of household-level violent child discipline and IPV initiated by both male and female partners. This expands the evidence base on heterosexual IPV, which typically focuses on men as perpetrators and women as victims.

This multi-region design and large cohort of couple-dyads enables a rigorous evaluation in a cRCT to measure the effectiveness of the REAL Fathers intervention. The cRCT design and progressive rollout across multiple cohorts will allow for timely adaptations to the program model based on emerging experiences and lessons learned as it scales out to more communities. Findings from this trial will inform future research and programs designed to address intergenerational cycles of violence that impede healthy child development. Our research team will partner with an advisory committee of ministry stakeholders to ensure policy relevance in the national and regional Ugandan policy space to promote sustainability and scale. Ultimately, this study will contribute valuable evidence on how this social and behavior change intervention reduces rates of violence against children, intimate partner violence, and improving child and family wellbeing, while providing an opportunity to investigate the clustering of multiple forms of violence within the household context and their connections to early childhood development.

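### Region-stratified models each rest on eight randomised sub-counties, and the stated inference is anti-conservative at that number unless a small-sample reference is used

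*Protocol article*

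**What the plan says.** All references are to the protocol article. The abstract gives "48 sub-counties randomly sampled from 24 districts in six regions of Uganda", and Study setting {9} places "four districts in each region". Under Sequence generation {16a}, "in each district, a simple random sample of two sub-counties will be taken", and "These sub-counties will be randomly allocated to either the treatment or control condition (1:1 within each district"). Table 7 lists the result: 24 districts, each with one intervention and one control sub-county.

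For the model, Statistical methods {20a} states that "we will incorporate random effects in the DID regression models to address clustering at the sub-county level". It adds clustered standard errors for correlation within individuals and within villages. The displayed equation has a sub-county random intercept and fixed effects of group, time and their interaction. It has no sub-county-by-time term.

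The additional-analyses section {20b} commits to regional stratification after all cohorts: "stratified analyses by region will be conducted to provide policymakers and program implementers more detailed information on intervention effects". The Discussion goes further: "The trial is also powered to stratify analyses by region". No reference distribution, degrees of freedom or small-cluster correction is given for the regional models.

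**The concern.** Information about a randomised effect is limited by the number of randomised units, however many couples each contains. Splitting the data by region leaves eight units per model. Mixed-model Wald tests and sandwich standard errors are justified for many clusters. With four per arm the estimated variance is biased downwards and highly variable, and a normal critical value allows for neither.

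The quantity that matters is how far sub-counties differ in their change over time. A random intercept absorbs differences in level, which largely cancel from a difference-in-differences contrast. It does not absorb differences in change.

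Regional results are singled out for regional programming and policy. If their intervals are too narrow, effects will be reported for regions that have none.

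**Working it through.** **Inputs.** 24 districts / 6 regions = 4 districts per region; 4 x 2 sub-counties = 8 per region; 1:1 within district gives 4 per arm. Check: 48 / 6 = 8. Table 6 shows a randomisation step in each cohort, but nowhere does the article give more than 48 sub-counties. The overall level is 5%, or 0.0125 for each of four primary outcomes. The protocol states no error rate for regional tests, so there is no figure of its own to reproduce.

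**Formula.** With balanced clusters the difference-in-differences estimate is a difference between two means of four sub-county changes. The unbiased variance has 4 + 4 - 2 = 6 df. The sandwich variance clustered on sub-county equals the unbiased variance times 3/4, and times 8/7 if the usual G/(G-1) factor is applied. For critical value c, assuming roughly normal sub-county mean changes, the true size is therefore P(|t6| > c x sqrt(3/4 x 8/7)).

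| Test, 4 v 4 sub-counties | Nominal 5% | Nominal 1.25% |
|---|---|---|
| Sandwich, no G/(G-1), normal | 14.1% | 7.4% |
| Sandwich with G/(G-1), normal | 11.95% | 6.0% |
| Unbiased variance, normal | 9.8% | 4.7% |
| Sandwich with G/(G-1), t on 7 df | 7.1% | 2.1% |
| Unbiased variance, t on 6 df | 5% | 1.25% |
| Same as row 2, all 48 sub-counties | 5.9% | 1.7% |

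Simulated binary data for eight sub-counties with six villages each gave 11.6% to 12.9% for row 2 at 5%. This hardly changed with the assumed variance components. A paired t on the four district differences (3 df) gave 5.0% to 5.3%.

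**Village-level clustering, as the protocol names it.** This was simulated without the sub-county random intercept, over an assumed range for the sub-county-by-time SD on the logit scale. Assumed SDs were 0.3 (sub-county), 0.6 (village), 0.4 (village by time) and 1 (individual).

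| Sub-county-by-time SD | Size at nominal 5% |
|---|---|
| 0 | about 6% |
| 0.15 | about 8% |
| 0.3 | 15% to 16% |
| 0.5 | 23% to 25% |

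**Six regions together.** With no effect anywhere and row 2 in each region, the chance of at least one false regional effect is 1 - 0.8805^6 = 53%. With valid 5% tests it is 1 - 0.95^6 = 26%.

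**Degrees of freedom for a pooled model.** Ignoring pairs: 48 - 12 = 36 (critical value 2.03). Respecting district pairs: 24 - 6 = 18 (2.10). Region-only: 6 df (2.45), or 3 df paired (3.18).

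**Cost of pooling the variance.** Suppose one region's sub-county SD is 1.5 times that of the other five. The pooled variance is (5 + 2.25)/6 = 1.208, so that region's standard error is too small by a factor sqrt(2.25/1.208) = 1.365. In simulation its size was about 14% (14.6% with 36 df, 14.3% with 18 df), and about 3% in each other region.

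**The case against.** The strongest reply is that 12% is not the error rate of the protocol's test. A reader might infer that it is, but the documents do not support that. The figure belongs to a sub-county sandwich with a normal reference, whereas the protocol combines a sub-county random intercept with village-level clustering and names no reference distribution. Its actual size could be lower or higher. This objection stands, and the figures are conditional.

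A second reply is that a reference distribution is analysis-plan detail. The protocol promises that an analysis plan will be registered and published before analysis, and that plan is not shown. It may contain a correction, so nobody can say that the regional intervals will be too narrow. What the protocol itself fixes is stratification into eight-cluster models, a large-sample model form, and the claim that the trial is powered for this use.

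A reader might also infer that no valid region-only test exists, because four pairs allow only 2^4 = 16 allocations and the smallest two-sided randomisation p-value is 2/16 = 0.125. That limit is real for a randomisation test, but t with 6 df or paired t with 3 df holds about 5%. Stratification alone is therefore not the error. The missing small-sample reference is.

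Third, pooling the variance across culturally diverse regions is a choice with a cost, as the 14% result shows. That is fair. The additional-analyses section already plans hierarchical cross-region models for each cohort, so a joint model is in keeping with the design. Finally, the section states no regional test or declaration rule, so over-declaration is a risk and not a stated intention.

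**Conclusion.** The point holds in conditional form. Each regional model has eight randomised sub-counties, and the stated approach is anti-conservative at that number unless a small-sample reference is added. For a sub-county-clustered test at nominal 5%, the true size is about 7% with t on 7 df and 12% to 14% with a normal reference, against 5.9% for the normal test on 48 sub-counties. Under village-level errors the size cannot be fixed from the document; over the assumed range it runs from about 6% to 25%.

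The sub-county figures assume balanced clusters and roughly normal sub-county mean changes. The main effect is little touched by the small number of clusters. This should be changed before regional results are produced, because they are meant to inform policy.

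**What to change.** State in the analysis plan that regional effects come from one model on all 48 sub-counties, with region-by-arm-by-time terms and a component for sub-county variation in change. Use a t reference or an established small-sample correction with cluster-level degrees of freedom: 18 if district pairs are respected, 36 if not. The small-sample reference is the essential part.

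Beside each pooled result, report a region-only interval (t with 6 df, or paired t with 3 df) as a check on the common-variance assumption. Describe regional results as estimates with intervals.

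No new data are needed, only plan wording and code. Intervals will be wider than uncorrected ones. Relative to the row 2 multiplier, 1.96 x sqrt(6/7) = 1.81, and at equal variance, the multiplier rises by about 12% with 36 df (2.03/1.81), 16% with 18 df (2.10/1.81) and 35% for region-only t with 6 df (2.45/1.81). The pooled model relies on roughly equal sub-county variance across regions.

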### Methods in analysis to handle protocol non-adherence and any statistical methods to handle missing data {20c}

We will conduct per protocol analysis and compare it against intention-to-treat analysis. Dosing data will be captured through participant identifiers that will permit linkages between monitoring and evaluation data in order to permit intervention dose as an exposure variable as opposed to simply including the bivariate exposure of control or intervention. Missing data may arise in different ways including the participants declining to provide the information, dropout of the study, and errors in data capture by the data collectors. The mechanism underlying the missingness will be explored. If missing completely at random, complete case analysis will be done. Missingness at random of outcomes will be handled through augmented inverse probability weighting. Individuals with missing covariates will be included in analysis by including a missing-indicator variable for the covariate as an additional covariate in the regression model.

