### Sample size {14}

Sample size is based on calculations using the outcome measure of proportion of young fathers who apply positive parenting behaviors. Based on the pilot studies on REAL Fathers intervention in Uganda, and to ensure sufficient statistical power of sub-group analyses at the regional level to obtain the largest sample size necessary, we assume only 40% of the young fathers use positive parenting skills at baseline [40]. From pilot studies, the REAL Fathers intervention should improve this proportion by at least 10% (effect size on absolute scale) by the endline [40]. The sample size computation is based on the formula:$$n=\frac{[2*{\left({Z}_{\alpha /4}+{Z}_{1-\beta }\right)}^{2}*\overline{P }(1-\overline{P })]}{{({P}_{1}-{P}_{0})}^{2}}\times Deff$$where:

*n* = minimum sample size of individuals required per arm of study

*Z*_α/4_ = the critical value of the standard normal variate at significance level of α/4 (*α* is assumed to be 0.05 or 95% certainty for improvement in the four primary outcome indicators). By setting the critical *Z* value corresponding to an alpha level of 0.0125 (i.e., α/4), our sample size calculation adjusts for multiple outcome testing while maintaining an overall 5% level of statistical significance for the trial.

*Z*_1-β_ = the critical value of the standard normal distribution at a power of 1-β (assumed to be 0.80 or 80% power)

*P*_0_ = the value of positive parenting indicator at the baseline; assumed 40%

*P*_1_ = the value of positive parenting indicator at the endline; assumed to be 50%—a 10-percentage point increase based on pilot studies$$\overline{P } = \frac{{P}_{1}+{P}_{0}}{2}$$

*Deff* = clustering effect, assumed to be 2.3

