Based on the Uganda Bureau of Statistics 2019 population projections and Uganda Demographic and Health Survey 2016 data, only 4% of the male population (16–25 years) are young fathers who are married or cohabiting [6]. According to the latest Uganda population and housing census, the average village size is about 100 households [49]. Thus, no more than 10 young men (16–25 years) will be fathers whose eldest child is below the age of three years. To be on the conservative side, we assume that, on average, only 8 young fathers are eligible for the study from any given village. Let $$\overline{m }$$ denote this average and suppose *cv* is the coefficient of variation in the number of fathers across the different villages, and ρ is intra-cluster correlation (ICC). Pilot studies on the REAL Fathers intervention approximated ICC of 0.20–0.24 at the village level. Thus:$$Deff=\left(1+\left(\left({cv}^{2}+1\right)\overline{m }-1\right)\rho \right)=\left(1+\left(\left(0.063+1\right)\times 7-1\right)\right)\times 0.20=2.3$$

Based on the above parameters and an attrition rate of 10% between the baseline and endline, a total of 1872 couple dyads is required per study arm (3744 in total). This translates to 156 couples per district: 78 in each study arm from 6 villages; and 312 couples per geographical region. This makes an assumption of treatment effect size of 10% on indicators at project level and 80% statistical power and 95% certainty (alpha = 0.05).

The study is being conducted across regions characterized by diverse subcultures, both between and within locations. To ensure sufficient power to detect potential heterogeneity in treatment effects across key subcultural groups, we adjusted the sample size accordingly. Drawing on pilot data, we anticipate a moderate level of effect heterogeneity across these subcultures. According to Ford and Norrie (2016) [50] and Kent et al. (2018) [51], moderate heterogeneity corresponds to a coefficient of variation (CV) of approximately 20% in treatment effects. To account for this, we increased the originally planned sample size by 20%, resulting in a target of 2200 participants per study arm.

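### Complete-case analysis is triggered by a judgement of missing completely at random that the data cannot confirm; the AIPW already planned should be the default

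*Protocol article*

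**What the plan says.** Section {20c} of the protocol article names three sources of missing data: "Missing data may arise in different ways including the participants declining to provide the information, dropout of the study, and errors in data capture". It then sets a conditional rule, which starts from an examination of the data once they are in: "The mechanism underlying the missingness will be explored". One branch applies if that examination points to MCAR: "If missing completely at random, complete case analysis will be done". The other branch covers outcomes under the weaker assumption: "Missingness at random of outcomes will be handled through augmented inverse probability weighting". The section gives no criterion for deciding between the two branches.

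Three other statements bear on the point:
- Section {20a} sets an intention-to-treat primary analysis in which "all study participants will be analyzed according to their original randomization assignment at baseline". It uses a mixed-effects logistic difference-in-differences (DiD) model whose printed equation has one random effect, for sub-county.
- Section {14} allows for "an attrition rate of 10% between the baseline and endline".
- Section {21b} plans interim analyses on Cohorts 1 and 2 and final analyses on the full dataset.

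**The concern.** The handling of missing outcomes is chosen after the missingness has been examined. A check on observed data can reject MCAR, but a check that finds nothing does not establish it. It may have had little power, and no check can see dependence on the outcomes that are missing. The rule therefore lets an absence of evidence select the method with the stronger assumption, although a method with a weaker assumption is already in the plan.

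Two of the three named sources, refusal and dropout, can plausibly depend on participant characteristics. The trial is open-label ({17b}) and concerns partner violence and harsh discipline, so dropout could also differ by arm. Complete-case estimates could then be off, and the method could change between the interim and final reports.

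**Working it through.** The rule rests on no figure in the protocol, so there is none to reproduce. What can be checked is how large a wrong choice would be.

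**Inputs from section {14}:** 1872 couples per arm, 3744 in total; 10% attrition, or about 187 couples per arm; proportions of 40% and 50%, the latter "assumed to be 50%—a 10-percentage point increase based on pilot studies". **Assumptions not in the document:** how strongly a baseline factor predicts the outcome, and how dropout varies with it.

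**Formula.** With attrition d, the full-arm mean is (1 − d) × completer mean + d × dropout mean. The error in the completer mean is therefore d × (completer mean − dropout mean).

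**Case A: 8% versus 12% dropout across a 50:50 factor.**
- Share with the higher-dropout level: 0.06/0.10 = 60.0% of dropouts and 0.44/0.90 = 48.9% of completers, a difference of 11.1 points.
- Factor shifts the outcome by 20 points: gap 0.111 × 20 = 2.2 points; error 0.10 × 2.2 = 0.22 points in that arm.
- Factor shifts the outcome by 40 points: gap 4.4 points; error 0.44 points.
- If the pattern and the factor's effect are the same in both arms, the errors cancel in the risk difference.

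**Case B: dropout depends on the baseline outcome, in opposite directions in the two arms.** Baseline 40% in both arms, endline 40% and 50%, and endline risk 40 points higher in those positive at baseline. The true effect is 10.0 points.

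For 8/12%, the share positive at baseline among completers is:
- intervention: 0.40×0.92/(0.40×0.92 + 0.60×0.88) = 0.368/0.896 = 41.1%
- control: 0.40×0.88/(0.40×0.88 + 0.60×0.92) = 0.352/0.904 = 38.9%

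The difference is 2.13 points. The endline difference is 10 + 0.40 × 2.13 = 10.9. A DiD restricted to couples seen at both waves gives 10.85 − 2.13 = 8.7.

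| Dropout by baseline status | Completers positive at baseline (intervention / control) | Endline difference | DiD, couples seen at both waves |
|---|---|---|---|
| 8/12% | 41.1% / 38.9% | 10.9 | 8.7 |
| 7/13% | 41.6% / 38.4% | 11.3 | 8.1 |
| 5/15% | 42.7% / 37.4% | 12.1 | 6.8 |

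The endline difference is about 1 to 2 points too high. The restricted DiD is 1.3 to 3.2 points too low.

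A simulation of the same set-up (2,000 runs, 1872 per arm, no clustering) gave endline differences of 10.9, 11.2 and 12.2. Standardising on baseline outcome by arm, as a stand-in for a MAR-valid method, gave about 10.0 each time. With 10% dropout everywhere, so that MCAR holds, the SD of the estimate was 0.0168 standardised and 0.0170 for complete cases.

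In those runs, two simple 5% checks (missingness against arm, and against baseline outcome) flagged a departure in 19%, 27% and 57% of runs. The flag rate was about 10% when MCAR was true. The reversal between arms hides the pattern from a pooled check; a check within arm would see more.

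**The case against.** If MCAR is true, complete cases are unbiased and need neither a missingness nor an outcome model. AIPW needs at least one of these to be right and has to be combined with a clustered logistic DiD. The equal precision in the simulation came from a simple stand-in without clustering, so it does not show that AIPW is free of cost here. Case B also rests on assumptions absent from the document. All of this stands, and it limits the size of the point. It does not justify a branch entered on a judgement that cannot be verified.

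Three stronger readings are tempting, and the document does not support them.

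- **A check in one cohort would wrongly choose complete cases about two times in three.** For 8% versus 12% dropout by a 50:50 factor, a two-sided 5% test with the design effect of 2.3 has 77% power with 3744 couples and 34% with 1248. Without the design effect the figures are 98% and 65%. The protocol names no single-covariate test at 0.05. It gives the 2.3 for the sample-size outcome, not for dropout. It does not state three equal cohorts, and the per-cohort numbers in section {8} are unclear.
- **A 2-point bias would usually go unnoticed.** From an observed 50:50 factor with a 40-point effect in one arm, 2 points needs about 1% versus 19% dropout: 95% of dropouts against 45% of completers at the higher-dropout level, a 20-point gap, times 0.10. The same test detects this more than 99% of the time even in 624 couples (one arm of one third of the sample) after the design effect. If the gap is not explained by observed data, AIPW would not remove it either.
- **The primary estimator is not fixed in advance.** Section {20a} fixes the intention-to-treat DiD mixed model. Only the handling of missing outcomes is conditional, and both branches are named.

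How MCAR would be judged may be left to an analysis plan that is not shown. The conditional rule itself is stated in the protocol, and a plan that follows it would inherit the problem.

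**Conclusion.** The concern holds as a weakness in the rule. The method for missing outcomes depends on a judgement that data can contradict but not confirm, and a wrong judgement leads to the method with the stronger assumption. At 10% attrition the expected bias is modest: about 0.2 to 0.4 points in an arm mean in Case A, and 1 to 2 points in the endline difference only under the strongly prognostic, arm-reversed dropout of Case B. These figures show direction and scale and are not predictions. Errors grow with attrition; the document gives no attrition figure for the follow-up wave, so none is computed for it.

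AIPW corrects only for dropout explained by observed predictors, given a correct missingness or outcome model. It does not address dropout that depends on unseen violence or engagement.

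**What to change.** In section {20c}, delete the sentence that sends data judged MCAR to complete-case analysis. State that AIPW, or an equivalent MAR-valid method using the baseline outcome and other baseline predictors of dropout, is the primary handling of missing outcomes in all interim and final analyses, whatever the exploration of missingness shows. Report complete cases as a sensitivity analysis. Cover dropout that depends on unobserved outcomes by a separate missing-not-at-random sensitivity analysis.

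The sample size does not change. The text change is about one sentence, and AIPW is already planned. The real cost is the modelling needed to combine AIPW with the clustered DiD model. Section {31c} commits to registering and publishing the analysis plan before data analysis begins, so the change belongs there as well.
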